## Abstract

The prevalence of coronary artery disease (CAD) in patients with severe aortic stenosis (AS) is 30–68%. Nevertheless, there is still not enough evidence to use invasive assessment of lesion severity, because the hemodynamic milieu of AS may impact the fractional flow reserve (FFR) and non-hyperemic indices. Therefore, the aim of the study is two-fold. First, to measure acute and long-term changes of FFR, index of microvascular resistance (IMR), and coronary flow reserve (CFR) in patients undergoing TAVI procedure. Second, to compare the diagnostic accuracy of intracoronary indices with myocardial perfusion measured by cadmium-zinc-telluride single-photon emission tomography (CZT-SPECT) and find cut-off values defining significant stenosis. We plan to enroll 40 patients eligible for TAVI with intermediate stenosis (30–70%) in the left anterior descending (LAD) coronary artery. In each patient FFR, CFR, and IMR will be measured in addition to myocardial blood flow calculated by CZT-SPECT before and either immediately after TAVI (acute cohort) or in 6 months (late cohort) after the procedure. FFR, CFR, and IMR will be matched with the results of myocardial perfusion measured by CZT-SPECT in the area of LAD. As a result, cut-off values of FFR, CFR, and IMR defining the decreased blood flow will be found.

## 1. Introduction

Aortic stenosis (AS) is the most common valvular disease, and the number of patients is set to double in the next 20 years [1]. Importantly, in 30–68% of patients diagnosed with AS, coronary artery stenosis is also present [2].

In clinical practice, the severity of coronary artery stenosis and microvasculature dysfunction can be assessed by means of fractional flow reserve (FFR), coronary flow reserve (CFR), and index of microvascular resistance (IMR). However, in patients with AS, the assessment of coronary flow is impaired due to volume and pressure overload of the left ventricle. Moreover, in patients with AS and concomitant coronary artery disease (CAD) not a single stenosis but tandem stenosis is present—first is the aortic stenosis, and second is the coronary artery stenosis. As a result, the hyperaemic flow in coronary arteries is changed which affects the measurement of coronary artery hemodynamics [3].

Transcatheter aortic valve implantation (TAVI) allows the rapid unloading of the left ventricle and can acutely affect coronary flow. As reported by Pesarini et al. and Lunardi et al., changes in FFR after transcatheter aortic valve implantation (TAVI) were insignificant, indicating that this tool can be used to guide revascularisation in AS patients [4,5]. On the other hand, the underestimation of coronary stenosis by hyperemic indices was found in most of the studies conducted so far [6,7,8,9,10]. The discrepancy between findings and lack of evidence is reflected in current guidelines, which still maintain coronary angiography as a standard to guide revascularization [11,12].

All things considered, the physiological assessment of intermediate coronary artery stenosis severity in patients with severe AS is still a real challenge. Therefore, the aim of this study is to investigate the changes in FFR, CFR, IMR, and myocardial perfusion in patients with severe AS after TAVI. As a first endpoint, we will assess acute and long-term changes in FFR, IMR, and CFR in patients undergoing the TAVI procedure. The secondary endpoint is to determine cut-off values of intracoronary indices defining significant stenosis based on myocardial perfusion measured by cadmium-zinc-telluride single-photon emission tomography (CZT-SPECT), in patients with severe AS and concomitant CAD.

## 2. Materials and Methods

### 2.1. Study Design

We are planning to enroll 40 patients, all of whom have a clinical indication to elective TAVI, as jointly evaluated by the local Heart Team, and are diagnosed with intermediate stenosis (30–70%) in the left anterior descending (LAD) artery. We will measure FFR, CFR, and IMR before, and either immediately after (Group I) or 6 months after (Group II) TAVI. At the same time, myocardial perfusion will be assessed by CZT- SPECT, to compare intravascular indices to myocardial perfusion results (Figure 1).

### 2.2. Study Objectives

The primary objective is to measure FFR, CFR, IMF, and myocardial perfusion CZT-SPECT before the TAVI procedure and either immediately after TAVI or after 6 months, to specify the acute and long-term changes in coronary pressure and flow. The secondary objective is to compare FFR, CFR, and IMR to myocardial perfusion CZT-SPECT to identify cut-off values of CFR, IMR, and FFR defining significant stenosis (Figure 2).

### 2.3. Population

Patients referred to TAVI with the present intermediate stenosis in LAD are eligible for the study. The exclusion and inclusion criteria are summarised in Table 1. As we are interested in the influence of left ventricle volume overload decrease after TAVI, only LAD will be assessed.

### 2.4. Sample Size

Our target sample size is set at 40 patients for a proof-of-concept study. No power calculations were performed since this is currently a pilot study and relevant data on our research objectives regarding the comparison between patients suffering from AS with CFR and IMR assessment are lacking. The results of this study will be used to design a larger study in the near future. Since the total number of patients for AS diagnosis in the Division of Cardiology and Structural Heart Diseases is estimated at 100 a year, we expect that our target number of patients can be included within one year.

### 2.5. Patient Recruitment

When all inclusion criteria are met, the patient will be asked by the physician to participate in the study. After signing the informed consent, each patient will undergo rest and stress CZT-SPECT and coronary angiography with measurement of FFR, CFR, and IMR. This diagnostic process will be repeated immediately after TAVI (Group I) or 6 months later (Group II).

### 2.6. SPECT Protocol

We plan to perform a 1-day protocol. Patients will be instructed not to consume chocolate and caffeine products 24 h before the test. Dynamic MPI-SPECT will be performed on a dedicated CZT-SPECT camera (D-SPECT Cardio, Spectrum Dynamics Medical). After the patient’s heart positioning within the field of view with the use of intravenous administration of an initial dose of approx. 37 MBq of ^99m^Tc-MIBI, an intravenous bolus infusion of 3.5 MBq/kg of ^99m^Tc-MIBI at a rate of 1–2 cm^3^/s using an automatic syringe pump will start for the resting dynamic scan. After a 25 min delay, an 8 min resting static perfusion scan will be performed.

In the next stage, we will inject 0.4 mg of regadenoson for the stress phase. Regadenoson bolus will be flashed with 5 mL 0.9% NaCl and 1 min after the injection, a stress phase list-mode acquisition will start with the administration of a second bolus of ^99m^Tc-MIBI (10 MBq/kg or 3× resting dose) at peak hyperaemia. Then after a 25 min delay a stress static perfusion scan will be conducted. Rest-stress dynamic acquisitions will be completed in about 75 min. List-mode data will be rebinned into 32 frames consisting of 21 × 3 s, 1 × 9 s, 1 × 15 s, 1 × 21 s, 1 × 27 s, and 7 × 30 s frames. During the rest and stress phase, monitoring of heart rate and rhythm, blood pressure, pulse oximetry, and electrocardiography (ECG) will be performed. Myocardial perfusion will be reported based on a 17-segment model of the heart [13]. For each segment, a coronary flow reserve (CFR) will be calculated with dedicated software (Corridor 4DM, INVIA, USA).

### 2.7. FFR, CFR, IMR Protocol

During invasive coronary angiography, patients with an intermediate lesion in LAD will undergo a hemodynamic assessment with FFR, CFR, and IMR. The pressure wire (Pressure Wire X, Abbott, IL, USA) will be positioned distally to the stenosis to acquire FFR, CFR, and IMR measurements. After the administration of nitroglycerine (100–200 µm), hyperemia will be induced by infusion of adenosine (140 mg/kg/min). To measure mean transit time (T_mn_), a thermodilution curve will be obtained by using 3 injections of 4 mL of room temperature saline. Hyperemic proximal aortic pressure (P_a_), distal arterial pressure (P_d_), and hyperemic T_mn_ will be measured before and during hyperemia. CFR and IMR will be calculated with the Coroflow software (Coroventis, Uppsala, Sweden). The operator will be blinded to the results of baseline measurements and to the results of CZT-SPECT scans.

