#### 2.8.2. Index of Microvascular Resistance

Myocardial resistance is mainly determined by microcirculation which can be measured with a coronary guidewire and expressed as an Index of Microvascular resistance (IMR). The IMR is calculated by multiplying the distal coronary pressure (P_d_) by the T_mn_ of a saline bolus during coronary hyperaemia induced by intravenous adenosine [16].
$$\mathrm{IMR}=T_{\mathrm{mn}}\times {\;P}_{d}$$

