#### 2.8.3. Coronary Flow Reserve

CFR represents the vasodilator capacity of the coronary vasculature during hyperaemia. It investigates both epicardial and microvascular diseases but does not allow discrimination between them. CFR is calculated by dividing the T_mn_ of saline at rest by the T_mn_ of saline in hyperaemia induced by intravenous adenosine [3,17,18]
$$\mathrm{CFR}=\frac{T_{\mathrm{mn}}\mathrm{Rest}}{T_{\mathrm{mn}}\mathrm{Hyp}}$$

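### Both drug doses in section 2.7 carry wrong units: nitroglycerine is given as a length, and adenosine at 140 mg/kg/min would mean 7 to 14 g per minute in adults of an assumed 50 to 100 kg

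*Protocol article*

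**What the plan says.** Section 2.7 (FFR, CFR, IMR Protocol) is the only place in the article that gives a dose for either drug used in the invasive measurement. Both stand in one sentence. The nitroglycerine part reads "After the administration of nitroglycerine (100–200 µm"), and the adenosine part reads "hyperemia will be induced by infusion of adenosine (140 mg/kg/min").

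The later sections name the stimulus without a dose. Section 2.8.2 defines IMR "during coronary hyperaemia induced by intravenous adenosine", and section 2.8.3 defines the denominator of CFR as the transit time "in hyperaemia induced by intravenous adenosine". Section 2.5 has the measurement done twice per patient: "This diagnostic process will be repeated immediately after TAVI (Group I) or 6 months later (Group II"). The regadenoson dose in section 2.6 belongs to the stress phase of the CZT-SPECT scan and has no bearing on these two entries.

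**The concern.** The first entry has the wrong dimension. A micrometre cannot express an amount of drug, so a reader cannot recover a dose from it without guessing.

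The second entry is dimensionally valid, but it implies an infusion of grams of adenosine per minute in an adult.

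These are operating instructions, not background. Adenosine is the stimulus under which IMR and CFR are defined, and section 2.7 also has the proximal and distal pressures recorded during hyperaemia. Change in these indices is the primary objective in section 2.2. The patients have severe aortic stenosis, and each is to be measured twice. Section 2.4 adds that the results will be used to design a larger study, so a wrong dosing line in print could be carried forward.

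**Working it through.** There is no calculation in the article to reproduce. Section 2.4 says "No power calculations were performed since this is currently a pilot study", and neither dose feeds a sample size or a test. The check is of units and scale.

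**Inputs**
- Nitroglycerine: 100–200 µm (section 2.7).
- Adenosine: 140 mg/kg/min (section 2.7), intravenous (sections 2.8.2 and 2.8.3).
- Patients: 40 (sections 2.1 and 2.4), each measured before TAVI and once after it (section 2.5).
- Body weight: not given. Assumed range 50 to 100 kg.

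**Nitroglycerine.** µm is a length. No conversion to mass exists, so there is no interpretable dose.

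**Adenosine as printed.** Total rate = rate per kg × body weight.

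| Assumed weight | Calculation | As printed | If micrograms were meant |
|---|---|---|---|
| 50 kg | 140 × 50 = 7,000 | 7.0 g/min | 7.0 mg/min |
| 70 kg | 140 × 70 = 9,800 | 9.8 g/min | 9.8 mg/min |
| 100 kg | 140 × 100 = 14,000 | 14.0 g/min | 14.0 mg/min |

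The last column is 1,000 times lower. It rests on an assumption about the intended unit that the article does not confirm.

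**Does the result depend on the assumed weight?** No. The printed rate falls below 1 g/min only for a body weight under 1,000 / 140 = 7.1 kg, so any adult weight gives grams per minute.

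**Volume, for illustration only.** Solution strength is not in the article. At 70 kg, an assumed 1 mg/mL needs 9,800 / 1 = 9,800 mL/min, and an assumed 50 mg/mL needs 9,800 / 50 = 196 mL/min. The conclusion does not rest on these strengths.

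**Sessions the line describes.** 40 patients × 2 = 80 planned sessions. This counts planned measurements, not exposures to a wrong dose.

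**The case against.** The strongest reply is that this is an editorial matter. No endpoint, sample size, cut-off or test depends on either unit. The agent, the per-kilogram basis and the intravenous route are all stated, so the stimulus is mislabelled and not undefined. The article condenses a full protocol that is not shown, staff would presumably dose from that document, and trained operators would notice both slips. All of this stands, and it limits the practical risk. It does not make the printed figures right, and they are stated figures, not details left to a longer document.

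A second reply is that the two halves are not equally strong. The nitroglycerine unit is wrong on its face, whereas calling the adenosine rate wrong needs an assumed body weight and a judgement of what can be infused. That is fair as to the route of proof. The margin is so wide, however, that no adult weight rescues the figure.

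A third reply is that the text was read from PDF by a program, and a µ misread as m would give exactly the printed adenosine unit. This cannot be fully excluded. It is unlikely, because the µ sign survives earlier in the same sentence, and such a misreading would not explain the nitroglycerine unit, where the µ is intact and the wrong letter follows it.

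**Conclusion.** The concern holds. As printed, section 2.7 gives no usable nitroglycerine dose, and it gives an adenosine rate of 7.0 to 14.0 g/min over an assumed 50 to 100 kg. Nothing elsewhere in the article corrects either entry.

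That the units are wrong is firm. That micrograms were meant is an inference, probable but unconfirmed. Whether the operative protocol has the same slip cannot be judged from the article. The consequence is one of patient safety and of a correct published method; the statistical design and analysis are unaffected. It should be fixed, but it is not a reason to hold up the trial unless the operative protocol proves to carry the same error.

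**What to change.** Check both entries against the full protocol and the product information. Then correct two units in the one sentence of section 2.7, leaving the rest as it stands:

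- Nitroglycerine: 100–200 [confirmed mass unit], in place of µm.
- Adenosine: 140 [confirmed mass unit]/kg/min, in place of mg/kg/min, with the intravenous route added so that the sentence agrees with sections 2.8.2 and 2.8.3.

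The confirmed unit is probably micrograms in both places, but it should come from the source document and not from this inference.

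Publish the correction as an erratum to the article. Amend the operative protocol only if it carries the same slip, in which case an administrative amendment is enough. No procedure, visit or analysis is added.

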### 2.8. Calculation of FFR, IMR, and CFR

#### 2.8.1. Fractional Flow Reserve

Fractional flow reserve (FFR) is calculated as a ratio of pressure measured distally to the stenosis (P_d_) and in the aorta (P_a_) [14,15].
$$\mathrm{FFR}=\frac{P_{d}}{P_{a}}$$

#### 2.8.2. Index of Microvascular Resistance

Myocardial resistance is mainly determined by microcirculation which can be measured with a coronary guidewire and expressed as an Index of Microvascular resistance (IMR). The IMR is calculated by multiplying the distal coronary pressure (P_d_) by the T_mn_ of a saline bolus during coronary hyperaemia induced by intravenous adenosine [16].
$$\mathrm{IMR}=T_{\mathrm{mn}}\times {\;P}_{d}$$

#### 2.8.3. Coronary Flow Reserve

CFR represents the vasodilator capacity of the coronary vasculature during hyperaemia. It investigates both epicardial and microvascular diseases but does not allow discrimination between them. CFR is calculated by dividing the T_mn_ of saline at rest by the T_mn_ of saline in hyperaemia induced by intravenous adenosine [3,17,18]
$$\mathrm{CFR}=\frac{T_{\mathrm{mn}}\mathrm{Rest}}{T_{\mathrm{mn}}\mathrm{Hyp}}$$

#### 2.8.4. Calculation of Myocardial Blood Flow by SPECT

The time-activity curves (TAC) for the input function will be derived automatically after correction for motion artefacts. As a first step, to calculate myocardial retention rate a previously described model will be used [19]. As a second step, to convert the retention rate to myocardial blood flow values, the Renkin–Crone flow model will be used [19]. In the end, CFR will be calculated by dividing MBF in stress by MBF in rest. As a next step, the CFR measured by CZT-SPECT will be matched with FFR, CFR, and IMR calculated in LAD.

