### 2.9. Statistical Analysis

Normally distributed quantitative variables will be presented with mean, standard deviation, and 95% confidence interval. Non-normally distributed data will be presented with median and interquartile ranges. The difference between intracoronary indices values before and after TAVI will be assessed with Student *t* or Mann–Whitney *U* tests as appropriate. Sensitivity, specificity, positive predictive value (PPV), and negative predictive value (NPV) of intracoronary indices measured in LAD will be calculated on a per-patient basis. Receiver operator characteristic (ROC) curves will be constructed for FFR, CFR, and IMR to determine diagnostic cut-off values. Correlations between intracoronary indices and MBF measured by CZT-SPECT will be assessed using Pearson’s correlations. A statistically significant difference will be defined as a two-sided *P* value less than 0.05. The missing data will be labelled.

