It was previously found that FFR is underestimating coronary stenosis severity in patients before TAVI because it decreases within the same coronary lesion after the TAVI procedure [6]. Some studies reported that the change in FFR after TAVI is minor. However, as underlined by Vendrik and colleagues, these minor discrepancies are the main challenge in borderline FFR results. At the same time, these borderline lesions are also the most challenging in ICA assessment. Therefore, the main problem remains unsolved. Currently, several ongoing trials will compare FFR-guided revascularization to angiography-guided revascularization in patients with severe-AS (FAITAVI (Functional Assessment in TAVI); (NOTION-3)) which hopefully will shed light on further management of patients with severe AS and concomitant CAD. Unfortunately, none of these trial implements offer invasive indices or non-invasive imaging methods which may improve the assessment of coronary artery stenosis.

In patients with severe AS, an increased resting flow enables adequate perfusion at rest, but not during stress. That was reflected in previous studies which showed that resting blood flow velocity in patients with AS is almost 18% higher and hyperaemic flow is 34% lower as compared to the control group [27,28]. Consequently, the increased baseline flow and reduced hyperaemic flow result in CFR reduction. As far as IMR is concerned, the decrease in myocardial resistance at rest has been demonstrated in patients with AS [29]. However, there was no difference between the control group and patients with AS in hyperaemic IMR values [30]. As explained by Lumley and colleagues, ischemia in patients with severe AS was not caused by microvascular dysfunction, but by abnormal coronary coupling which affects both FFR and CFR, but not IMR [30]. All things considered, the effect of AS on coronary flow and microvasculature still needs to be clarified.

In previous studies, FFR was validated against myocardial perfusion SPECT, revealing a cut-off value higher than in patients without severe AS [31]. Importantly, so far a semiquantitative SPECT was used which does not allow for myocardial blood flow quantification. In our study, CZT -SPECT will be applied which provides a quantitative analysis of myocardial blood flow and myocardial flow reserve (MFR) which provides a more accurate assessment of multivessel and microvascular disease [32,33].

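### The FFR, CFR and IMR cut-offs are labelled as thresholds for significant stenosis, but the SPECT flow reserve they are matched to is not specific to stenosis, and IMR is a microvascular index

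*Protocol article*

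**What the plan says.** **Target condition.** Section 2.2 gives the secondary objective as comparing the three invasive indices with CZT-SPECT "to identify cut-off values of CFR, IMR, and FFR defining significant stenosis". The Introduction says the same and bases it on SPECT perfusion. The Abstract uses both labels: significant stenosis in its statement of aims and decreased flow in its closing sentence. Section 5 (Conclusions) joins the two in one phrase.

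**Comparator.** Section 2.8.4 computes SPECT CFR as stress flow over rest flow and then states that "the CFR measured by CZT-SPECT will be matched with FFR, CFR, and IMR calculated in LAD". Section 2.9 plans ROC curves for all three indices to obtain the cut-offs.

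**What the article says about these quantities.**
- On CFR, section 2.8.3: "It investigates both epicardial and microvascular diseases but does not allow discrimination between them".
- On IMR, section 2.8.2: "Myocardial resistance is mainly determined by microcirculation".
- On aortic stenosis (AS), section 3: "the increased baseline flow and reduced hyperaemic flow result in CFR reduction".

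**The concern.** A diagnostic cut-off carries the meaning of the reference it was derived against. If the reference is low flow reserve, the cut-off predicts low flow reserve. It can be called a stenosis threshold only if low flow reserve in these patients indicates a significant LAD lesion. The article gives two reasons why it need not: microvascular disease lowers flow reserve too, and so does AS, which every participant has in severe form.

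IMR has the opposite problem. It is introduced as a measure of the microcirculation, yet a value of it is meant to define an epicardial lesion.

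The label matters beyond this pilot. The Discussion says the indices might guide revascularisation decisions, and section 2.4 says the results will be used to design a larger study. A threshold that partly reflects AS or microvascular disease would enter both under the name of stenosis.

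**Working it through.** The article states no size for the fall in CFR and makes no power calculation, so there is no figure of its own to reproduce. The check is mainly a comparison of sections, with one short calculation.

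**1. Does the limitation in section 2.8.3 apply to the SPECT quantity?** That section concerns invasive CFR, which is resting transit time divided by hyperaemic transit time. Shorter transit time stands for higher flow, so this is a ratio of hyperaemic to resting flow. Section 2.8.4 defines SPECT CFR as stress flow divided by rest flow. The construct is the same and only the method of measurement differs. The inability to separate epicardial from microvascular disease therefore carries over. The Discussion also supports quantitative SPECT by its value in multivessel and microvascular disease, which is not an argument that it is specific to one LAD lesion.

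**2. Does AS move the reference?** The Discussion says it does, and gives two inputs:
- "resting blood flow velocity in patients with AS is almost 18% higher": factor about 1.18.
- "hyperaemic flow is 34% lower as compared to the control group": factor 1 − 0.34 = 0.66.

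If the two may be combined:

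| Reading | Calculation | Flow reserve relative to controls | Fall |
|---|---|---|---|
| Both changes, rest +18% | 0.66 / 1.18 | 0.559 | 44.1% |
| Both changes, rest +17% | 0.66 / 1.17 | 0.564 | 43.6% |
| Hyperaemic change only | 0.66 / 1 | 0.66 | 34% |
| Resting change only | 1 / 1.18 | 0.847 | 15.3% |

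The direction is the article's own. The size is derived here and depends on dividing a flow figure by a velocity figure.

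**3. What does such a shift do to a ROC analysis?** Suppose AS multiplies every participant's flow reserve by the same constant k. Patients keep their rank order. Classifying at k × c then gives the same positives and negatives as classifying the unshifted values at c, and the ROC curve does not change. A uniform shift does harm only if flow reserve is split at a value not adapted to AS. A shift that varies between patients also changes the ranking. In neither case does the shift make a low value specific to a stenosis.

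**4. Is an IMR cut-off for stenosis coherent?** Section 2.2 asks for an IMR value that defines stenosis. Section 2.8.2 says the resistance which IMR expresses is determined mainly by the microcirculation. The Discussion adds that the abnormal coupling in AS affects FFR and CFR but not IMR. Nothing in the article links IMR to the severity of an epicardial lesion, so the two sections do not fit together.

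**The case against.** **The SPECT classifier for the ROC curves is not named.** Section 2.8.4 speaks of matching, section 2.9 does not say which SPECT variable divides patients, and section 2.6 plans static rest and stress scans on a 17-segment model. A regional perfusion reading could be the classifier, and an article may leave that detail to the full protocol. This stands as a caution. SPECT flow reserve remains the most direct reading of section 2.8.4, and the IMR problem does not depend on it.

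**The target is already partly stated as reduced flow.** The close of the Abstract does so. But section 2.2, the Introduction and the aims in the Abstract say stenosis, and the Conclusions run the two together. This shows that the passages need reconciling.

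**Quantitative flow was chosen deliberately.** The Discussion contrasts it with the semiquantitative SPECT of earlier work. Replacing it with a relative LAD measure as the primary reference would give up that advantage. Non-LAD disease that does not require revascularisation is not excluded by Table 1, and a relative measure removes the AS effect only if that effect is similar across territories. This objection stands, so the relative measure belongs in a sensitivity analysis.

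**Stronger readings that a reader might infer, and why they fail:**
- *AS alone cuts SPECT flow reserve by 44%.* The two inputs are cited jointly to two references, describe different quantities, are not described as SPECT measurements, and use a control group that the article does not characterise.
- *Most participants would be labelled positive without any lesion effect.* This needs a SPECT threshold and a lesion-free flow reserve, and the article gives neither.
- *The ROC reference switches from flow reserve to MBF between sections 2.8.4 and 2.9.* The sentence in 2.9 reads "Correlations between intracoronary indices and MBF measured by CZT-SPECT" and concerns Pearson correlations, a separate analysis.
- *Invasive CFR will look falsely good and FFR falsely poor.* Invasive CFR does share the reference's construct. But the article reports that AS also affects FFR, so the direction of any distortion in its cut-off cannot be settled here.

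**Conclusion.** The mismatch between target and reference holds on the article's own statements. Cut-offs derived as section 2.8.4 describes would identify reduced LAD-territory flow reserve in patients with severe AS. They would not by themselves identify significant stenosis, and the IMR cut-off is mislabelled whichever SPECT variable is used.

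The conclusion for FFR and CFR assumes that SPECT flow reserve classifies patients in the ROC analyses. The size of the AS effect is indicative only: roughly 44% if the two published figures may be combined, and 34% or 15% if only the hyperaemic or only the resting change is counted. The finding does not depend on that figure, or on the absence of a stated threshold, because no threshold would make flow reserve specific to stenosis. The documents do not show that the planned quantitative reference must be abandoned. What changes is what the trial may conclude from it. This should be corrected before the cut-offs are reported.

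**What to change.** 1. **Restate the target condition** of the ROC analyses in section 2.2, the Introduction, the Conclusions and the aims in the Abstract as *reduced LAD-territory flow or flow reserve on CZT-SPECT*. This agrees with the closing sentence of the Abstract.
2. **Limit the interpretation.** State that CFR and IMR cut-offs will not be read as stenosis thresholds, and that IMR will be reported as describing the microvascular component.
3. **Add one LAD-specific sensitivity reference**, chosen before the data are seen: either LAD divided by non-LAD stress MBF in the same patient, or a reversible defect in LAD segments on the static scans. Repeat the FFR analysis against it. Similar cut-offs under both references would support attributing the FFR result to the lesion. A clear difference would point to a global effect such as that of AS.

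**Cost.** Items 1 and 2 are wording. Item 3 uses the 17-segment rest and stress data already planned in section 2.6, with no further imaging or radiation. Its drawback is lower sensitivity when non-LAD territories are diseased, so those patients should be flagged in that analysis. With 40 patients in all, the comparison of references will be descriptive.
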